### AEs and data and safety monitoring plan

All AEs are systematically recorded by study staff on an ongoing basis and undergo a thorough review by the Principal Investigator to ascertain any potential association with the intervention. Following each exercise session, AEs are actively screened by study staff, which assesses for the occurrence of any AEs or identify barriers hindering the subject’s continuation in the exercise protocol. Furthermore, these screenings are repeated during monthly check-ins with a study investigator. Oversight of this process is provided by an independent medical monitor, who is tasked with ensuring the safety of the study protocol. The PI and the medical monitor convene bi-annually for comprehensive discussions. Prior to each meeting, the medical monitor is furnished with an AE log for review. Within 1 week following the meeting, the medical monitor provides the investigators with conclusions drawn from the discussions. In the event of serious AEs surpassing an anticipated threshold, as determined by the independent medical monitor, further enrollment in the study is halted until an independent local regulatory board, comprising a Hepatologist, a Gastroenterologist, and another uninvolved physician, reaches a unanimous decision to continue the study with appropriate modifications, which are then subject to approval by the local IRB.

For the assurance of data quality, a trained member of the study team conducts bi-weekly data quality checks within the REDCap platform. These checks are subsequently reviewed on a quarterly basis by an independent data quality monitor within the Department of Public Health Sciences. Both the designated study team member and the independent data quality monitor collaborate in advising the research team on matters pertaining to participant accrual, retention, and the completeness of the data collected.

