Safety and tolerability	• Safety and tolerability will be evaluated in terms of adverse events (AE), physical exam, and changes in body weight and/or vital signs at weeks 4, 8, 12, 16

Abbreviations: AE, adverse event; ALT, alanine aminotransferase; Apo, apolipoprotein; ASCVD, atherosclerotic cardiovascular disease; AST, aspartate aminotransferase; CK, cytokeratin; CRP, C-reactive protein; DASI, duke activity score index; DXA, dual x-ray absorptiometry; ELF, enhanced liver fibrosis; FIB-4, Fibrosis-4 index; HOMA-IR, homeostatic model assessment for insulin resistance; IPAQ, international physical activity questionnaire; MASLD, metabolic dysfunction–associated steatotic liver disease; MASH, metabolic dysfunction–associated steatohepatitis; MR-S, magnetic resonance spectroscopy; NFS, NAFLD Fibrosis Score; PDFF, proton density fat fraction; PRO-C3, N-terminal type III collagen propeptide; PROMIS, Patient-Reported Outcomes Measurement Information System; VCTE, vibration-controlled transient elastography.

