### Exercise training (Arms 1 and 2)

American College of Sports Medicine (ACSM) Guidelines for Exercise Prescription,^52^ including the frequency, intensity, time and type principles, are being used to teach subjects how to perform moderate-intensity aerobic exercise training (40%–59% maximal heart rate). To ensure physiologic adaptation, we included a progressive lead-in period until the target exercise dose is reached by week 4 (Table 4). This successfully prevented injury in our previous exercise intervention in sedentary individuals with MASH.^11^ Aerobic exercise can be completed by walking, jogging, or with cardio equipment (eg, recumbent bike). To further prevent injury, each session includes a warm-up and cool-down with low intensity walking and dynamic stretches. The warm-up is 10 minutes in length and is composed of 5 minutes of walking at 30%–40% of maximal heart rate followed by 5 dynamic exercises including knee to chest, 10-yard lateral shuffle, bent over twist, calf sweeps, and leg swings. Each exercise session ends with a 5-minute cool down on the treadmill at 30%–40% of maximal heart rate.

**TABLE 4 T4:** Acclimation period of progressive exercise for W1–W4

Study arm (MET-min/wk)	Week 1	Week 2	Week 3	Week 4
Arm 1 (750)	300	450	600	750
Arm 2 (1000)	300	500	750	1000

Abbreviation: MET, metabolic equivalents of task.

The study exercise physiologist is revising the program as fitness changes; subjects progress in speed or difficulty to ensure correct exercise intensity. Every exercise session is directly supervised (either in-person or with A-V telehealth) by research staff with real-time heart rate monitoring. After each session, the completed exercise dose is calculated by intensity (METs) × frequency (1 session) × time (min). For example, a typical 45-minute session composed of (10-minute warm-up × 3.0 METS) + (30-minute brisk walking × 5.0 METs) + (5-minute cool down × 3.0 METs) =200 METs. From there, the study exercise physiologist can vary the frequency, intensity, time and type prescription to design the next session (Table 5). For example, if a subject only has 30 minutes, exercise intensity may be increased to slow jogging (6.0 METs) to progress toward the assigned dose. This format is repeated until the assigned summative weekly dose is achieved. At the conclusion of the 16 weeks intervention period, subjects develop a plan to continue to exercise after the trial ends with the assistance of the staff exercise physiologist.

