**TABLE 5 T5:** FITT prescription for each exercise study arm

Study arm (MET-min/wk)	Frequency (d)	Intensity	Time (min)	Type
Arm 1 (750)	3–5	Moderate-vigorous	22–45	Aerobic
Arm 2 (1000)	3–5	Moderate-vigorous	30–60	Aerobic

Abbreviation: MET, metabolic equivalents of task.

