### SOC (arm 3)

This group is receiving the best MASH clinical practices in accordance with practice guidelines.^53^ Because in-office hepatology counseling occurs every 12–24 weeks,^54^ standard counseling is happening at baseline and end-of-trial and is reinforced by American Liver Foundation handouts. This counseling includes information about completing at least 150 min/wk of physical activity as recommended by the ACSM.^8^ Physical activity is being measured remotely by fitness activity trackers like that in arms 1 and 2. Subjects randomized to SOC are given 16 weeks of fitness center membership and access to the study exercise physiologist for training sessions following completion of the study protocol.

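### AEs are actively screened after every exercise session in arms 1 and 2 but, in SOC, only at the 4-weekly visits, so an exercise-versus-SOC AE summary that pools session-found events is open to ascertainment bias against exercise

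*Protocol article*

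**What the plan says.** The section on AEs and data and safety monitoring describes three layers of AE capture:

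- General recording, with no arm named: "All AEs are systematically recorded by study staff on an ongoing basis".
- Active screening linked to sessions: "Following each exercise session, AEs are actively screened by study staff".
- A repeat at regular contacts, again with no arm named: "these screenings are repeated during monthly check-ins with a study investigator".

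The exercise section puts staff in contact with the participant at each session: "Every exercise session is directly supervised (either in-person or with A-V telehealth) by research staff". Table 5 ("FITT prescription for each exercise study arm") gives 3–5 days a week for arm 1 and the same for arm 2; the two doses differ in session time (22–45 against 30–60 minutes). SOC participants have no study sessions during the 16 weeks. The SOC section offers them "access to the study exercise physiologist for training sessions following completion of the study protocol".

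Table 2 schedules AE collection for all participants at every visit, so after baseline at weeks 4, 8, 12 and 16. Table 3 has a separate safety block: "Safety and tolerability will be evaluated in terms of adverse events (AE), physical exam, and changes in body weight" and vital signs, at those same four weeks. It does not say whether AEs found at session screens are counted.

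**The concern.** The number of AEs recorded depends on how often and how soon people are asked. A sore knee that lasts two days is likely to be reported to staff after that day's session and may be forgotten by a visit three weeks later. When one side of a randomised comparison is asked several times a week and the other once every four weeks, recorded rates of minor events can differ even if true incidence is the same.

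This matters because the eligibility section names musculoskeletal injury as an intervention-related risk of concern, and soreness, joint pain and fatigue are the events most sensitive to the frequency of asking. With 15 participants per arm, a few additional minor events can change how an AE table by arm reads. If the route of detection is not captured at collection, a later analysis cannot reliably separate a harm of exercise from a detection effect.

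**Working it through.** **1. Count of scheduled elicitations.** The document states no figure to reproduce, so this counts what it prescribes.

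Inputs: 16 weeks; 3–5 sessions a week in arms 1 and 2 (Table 5); one screen per session (safety monitoring section); four post-baseline visits with AE collection in all arms (Table 2); no sessions in SOC. The monthly check-ins are taken to be the 4-weekly visits.

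- Session screens: 3 × 16 = 48 to 5 × 16 = 80.
- Exercise total: 48 + 4 = 52 to 80 + 4 = 84.
- SOC total: 4.
- Ratio: 52/4 = 13 to 84/4 = 21.

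**2. Sensitivity of the count.** The lead-in in Table 4 starts at 300 MET-min/wk, and the exercise section puts a typical session at about 200, so the first weeks may hold fewer sessions. As an extreme, count no session at all in weeks 1–3: 3 × 13 = 39 screens, 39 + 4 = 43, ratio 43/4 = 10.75. If the monthly check-ins are instead four contacts additional to the visits in every arm, the totals are 56–88 against 8, ratio 7–11. The asymmetry is large on either reading.

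**3. Do the shared visits level it?** By each 4-weekly visit, an exercise participant has already been asked 3 × 4 = 12 to 5 × 4 = 20 times in the preceding four weeks. If events found at those screens are carried into the visit summary, the shared timing does not make ascertainment equal.

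**4. Illustration of direction (assumed model; no AE rates are given).** Suppose true incidence is identical in all arms and an event is reported at the next query with probability exp(−k × delay), where k = ln 2 / half-life. Mean capture for query interval T is (1 − exp(−kT))/(kT), with T = 28 days for SOC, 7/3 days at 3 sessions a week and 7/5 days at 5. For a 14-day half-life, k = 0.0495. SOC: kT = 1.386, capture 0.75/1.386 = 0.541. Three sessions a week: kT = 0.1155, capture 0.944. Ratio 1.75.

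| Recall half-life (assumed) | SOC capture | 3/wk | 5/wk | Ratio 3/wk to SOC | Ratio 5/wk to SOC | Ratio 5/wk to 3/wk |
|---|---|---|---|---|---|---|
| 3 days | 0.154 | 0.773 | 0.854 | 5.01 | 5.54 | 1.105 |
| 7 days | 0.338 | 0.893 | 0.934 | 2.64 | 2.76 | 1.046 |
| 14 days | 0.541 | 0.944 | 0.966 | 1.75 | 1.79 | 1.023 |
| 28 days | 0.721 | 0.972 | 0.983 | 1.35 | 1.36 | 1.012 |

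The model ignores spontaneous reports between visits, which would narrow the gap. The spread of results follows the assumed half-life, so it shows direction only and does not estimate the effect in this trial.

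**5. After the fix.** If the between-arm summary uses only answers to the common query at weeks 4, 8, 12 and 16, each arm has four elicitations: 4/4 = 1.0.

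**The case against.** The strongest reply is that the article plans no between-arm AE analysis. Safety is a separate block in Table 3, and the Data analysis plan does not mention AEs. A reader might infer that the safety end point is biased as it stands. The document does not support that: it names no AE contrast, times the evaluation at visits shared by all arms, and does not limit ongoing recording to the exercise arms. This part of the reply stands, and the point is conditional: the risk arises if session-found events are pooled into a summary by arm. It does not remove the point. The collection rule is stated, session-found events are not excluded, and even a descriptive AE table by arm invites the comparison.

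A second reply is that a detection-source field and a scripted question are case-report-form detail that a condensed article leaves out. That is fair, and either may already exist. If so, only the reporting rule is needed. For the same reason one cannot say that all AEs go into a single analysis log; the article mentions only a log supplied to the medical monitor.

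Third, a reader might infer a bias against the higher dose or against more frequent sessions. Table 5 prescribes the same 3–5 days a week in both exercise arms, frequency is not randomised, no analysis by frequency is planned, and the illustration gives only 1.012–1.105 for five against three sessions. Nor does SOC ascertainment bear on whether 1000 MET-min/wk is feasible; that is judged within arm 2, against arm 1 under the same screening, and from adherence.

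Fourth, the SOC section's statement that "standard counseling is happening at baseline and end-of-trial" might be read as showing sparse AE contact. It concerns lifestyle counselling; Table 2 shows AE collection in SOC every four weeks.

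Finally, screening after sessions protects participants and is natural in a supervised exercise trial. Agreed; nothing here argues for removing it.

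**Conclusion.** The point holds for exercise (arms 1 and 2) against SOC. As prescribed, active AE elicitation is about 52–84 occasions against 4 per participant, a ratio of 13–21. The ratio is lower if the lead-in weeks hold fewer sessions or if check-ins are separate from visits, but remains several-fold. An AE summary by arm that includes session-found events is open to ascertainment bias against exercise, mainly for minor, self-limiting events.

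The limits are equally clear. The size of any bias in AE rates cannot be derived from the document. Serious AEs, which drive the rule for halting enrolment, are less affected. The MRI-PDFF primary outcome is untouched. The design builds in no difference in session frequency between arms 1 and 2. The conclusion rests on two readings: that no scheduled SOC query exists beyond the contacts described, and that session-found AEs enter the Table 3 end point because nothing excludes them.

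**What to change.** - Keep the screening after each session unchanged, for participant protection.
- Add a field to the AE form for how the event was found: session screen, scheduled visit or spontaneous report.
- At the existing week 4, 8, 12 and 16 visits, ask every participant in all three arms the same scripted AE question about the preceding four weeks, answered without reference to the session records.
- Base the between-arm AE summary on events elicited by that question, plus all serious AEs.
- Report session-found AEs in a separate table for arms 1 and 2 only.

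The cost is one form field, one scripted question at visits already scheduled, and one extra table. The between-arm summary will contain fewer minor events. Exercise participants who have been asked repeatedly may still recall more at the visits; that residual priming cannot be designed away and should be noted when the AE results are reported. If participants have already completed visits, state from which date the field and question apply.

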### Data analysis plan

We will invoke the intent-to-treat principle for the primary analyses. We will apply an ANCOVA to compare the 3 groups with respect to the MRI-PDFF (primary outcome) and all other continuous secondary outcomes while including the baseline measurement and diabetes status as covariates. We impose a Bonferroni-corrected significance level of 0.017 for the multiple pairwise comparisons of the three groups. We will apply a Mantel-Haenszel test to compare the 3 groups with respect to dichotomous outcomes while accounting for the baseline measurement and diabetes status. A *p*-value of <0.05 will be regarded as statistically significant. As a series of secondary analyses and sensitivity analyses, we will use multiple imputations for estimating missing values in the outcomes variables to assess the robustness of the primary analyses. We will conduct all statistical analyses via SAS version 9.4 (Cary, NC).

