### Sample size and power calculations

We conservatively expect our 3 groups (SOC control vs. 750 MET-mins/wk vs. 1000 MET-mins/wk), to experience mean relative reductions in MRI-PDFF of −5%, −30%, and −40%, respectively, with a SD of 6% (30% or greater is considered clinically significant because this surrogates for histologic improvement).^56,57^ We based these assumptions on (1) our recent meta-analysis of 551 individuals with MASLD from 14 exercise-intervention studies for which −36% and −46% MRI-measured liver fat reduction was observed for 750 MET-min/wk, and 1000 MET-min/wk of exercise, respectively, alongside a +7% gain for SOC controls;^10^ and (2) our NASHFit Trial that found subjects who performed 750 MET-min/wk to experience a −30% reduction in MRI-PDFF compared to +11% for SOC control subjects.^11^ Lower doses of exercise were not chosen because <750 min/wk was found to have similar efficacy as SOC. Additionally, based on our previous experience, we also account for 20% of the subject drop-out in the power calculation, although we fully expect it to be much less.^58^ Based on pairwise comparisons with two-sided *t* tests in an ANCOVA setting, each with a significance level of 0.017 (Bonferroni correction), a sample size of 15 per group (total sample size=45) yields at least 90% statistical power for each pairwise comparison.

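### Fixed Bonferroni at 0.017 is valid but needlessly strict for three groups; a Shaffer step-down raises power for the 1000 vs 750 MET-min/wk contrast within the same 5% familywise error

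*Protocol article*

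**What the plan says.** Two sections of the protocol article set the level for pairwise comparisons, and they agree. Sample size and power calculations describes two-sided t tests in an ANCOVA setting, "each with a significance level of 0.017 (Bonferroni correction"). The Data analysis plan repeats it: "We impose a Bonferroni-corrected significance level of 0.017 for the multiple pairwise comparisons of the three groups".

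The Data analysis plan then gives the Mantel-Haenszel test for dichotomous outcomes and adds that a p-"value of <0.05 will be regarded as statistically significant". That sentence names no analysis.

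The planning assumptions, for SOC, 750 and 1000 MET-min/wk in that order, are "mean relative reductions in MRI-PDFF of −5%, −30%, and −40%, respectively, with a SD of 6" (per cent), with 15 randomised per group, 20% dropout and at least 90% power for each pairwise comparison. No step-down or closed procedure, and no gate through an overall test, is described.

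**The concern.** The abstract puts the required exercise dose at the centre of the trial's primary aim. On the planning means, the exercise arms differ from SOC by 25 and 35 points but from each other by only 10. A fixed penalty for three comparisons costs the two large contrasts almost nothing, so nearly all of it is paid by the dose contrast, which is the hardest to show.

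That penalty is avoidable in part. Among three groups, if one pairwise equality is false, at most one of the other two can be true. Once one difference has been established there is at most one true null hypothesis left to protect, and dividing alpha by three no longer serves a purpose.

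There is also a smaller point of wording. The 0.05 sentence has no stated scope. If someone applied it to three unadjusted pairwise tests, the familywise error would be well above 5%.

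**Working it through.** **Inputs, all from the protocol article.** Differences: 1000 vs 750 = 40 − 30 = 10 points; 750 vs SOC = 30 − 5 = 25; 1000 vs SOC = 40 − 5 = 35. SD 6%. Two-sided alpha 0.017 (0.05/3 = 0.0167, rounded). Evaluable per arm: 15 × 0.8 = 12. The ANCOVA has three group means plus baseline and diabetes status, so error df = N − 5, which is 36 − 5 = 31 at 12 per arm and 45 − 5 = 40 at 15 per arm.

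**Formula.** Noncentrality = difference / (SD × √(2/n)); power is the probability that a noncentral t exceeds the two-sided critical value.

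**Step 1: the plan's own figure.** For the 10-point contrast with a two-sample t test at 0.017:
- n = 12: noncentrality 10 / (6 × √(2/12)) = 4.08; power 92.3%.
- n = 11: power 89.2%.

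So 12 is the smallest number per arm that reaches 90%, and 12/0.8 = 15 per group. The total of 45 is reproduced exactly. With ANCOVA degrees of freedom, power at 0.017 is 93.4% at n = 12 and 97.8% at n = 15. The two contrasts with SOC have power of about 100%.

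**Step 2: the step-down.** Order the three p-values. Test the smallest at 0.05/3; if it is significant, test each of the other two at 0.05. Because the SOC contrasts pass the first step almost surely under the planning assumptions, the dose contrast is in effect tested at 0.05.

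| Evaluable per arm | SD | Bonferroni 0.017 | Step-down |
|---|---|---|---|
| 12 | 6% (article) | 93.4% | 97.7% |
| 15 | 6% (article) | 97.8% | 99.4% |
| 12 | 8% (assumed) | 70% | 84% |
| 12 | 10% (assumed) | 48% | 66% |
| 12 | 15% (assumed) | 20% | 35% |

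Only the first two rows use the article's SD.

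**Step 3: error control.** Simulation with 200,000 runs per scenario and error df N − 5:
- All three arms equal: familywise error 0.042 to 0.044 for the step-down, 0.043 to 0.045 for Bonferroni, about 0.12 for three ungated tests at 0.05.
- Two arms equal, third different: at most 0.0505 for the step-down, which is within simulation error of 0.05, and about 0.017 for Bonferroni.

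In the second case, with the two exercise arms as the equal pair, those figures are the type I error of the dose contrast itself: about 5% against about 1.7%.

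**Step 4: nothing is lost.** Any comparison rejected by Bonferroni at 0.05/3 is also rejected by the step-down. The only exception against the plan as written is a rounding one: the rounded 0.017 slightly exceeds 0.05/3 (3 × 0.017 = 0.051), so a smallest p between 0.0167 and 0.017 would pass the plan but not the step-down.

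**The case against.** Bonferroni is simple, valid and prespecified, and the trial was sized on it. The stated power is met, so nothing in the plan is wrong. At the only SD the article gives, the gain is about four points with 12 per arm and under two with 15. The larger gains need SDs that the article does not contain, and at SD 15% the step-down still leaves only 35% power, so it does not rescue a trial with a much larger SD. The article's own limitations section allows that there may be a threshold effect with no dose relationship; in that case Bonferroni guards the dose claim more strictly than the step-down does. Simple simultaneous intervals also come free with Bonferroni. All of this stands. It makes the point an optional efficiency gain, but it does not remove it, because the article's target of 5% across the three comparisons is met either way.

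A reader might go further and infer that the plan contradicts itself, with 0.017 and 0.05 both set for the pairwise tests, so that a pairwise p of 0.03 is both significant and not. The text does not support this. Both sections give 0.017 expressly for pairwise comparisons. The 0.05 sentence names no pairwise test, follows the Mantel-Haenszel sentence, and can be read as the level for the overall and dichotomous comparisons. It is an ambiguity of scope, and alone it would be a detail that a full analysis plan could settle.

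**Conclusion.** A cheap improvement, not an error. Under the article's assumptions (means −5, −30 and −40, SD 6%, 12 evaluable per arm), the step-down lifts power for 1000 vs 750 MET-min/wk from about 93% to 98%, and with 15 evaluable per arm from about 98% to 99%. The benefit becomes substantial only if the true SD is clearly above 6%, which is an assumption.

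It would be too strong to say that the step-down simply grants the dose contrast 0.05, or that it is free. The 0.05 level depends on the smallest p-value first passing 0.05/3, and if the dose contrast itself has the smallest p, it is tested at 0.05/3. There are also two real costs: the mismatch between intervals and tests, and the larger share of the 5% that the dose contrast uses when the exercise arms do not differ.

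**What to change.** In the Data analysis plan, replace the Bonferroni sentence with wording such as: *The three pairwise p-values will be ordered. The smallest will be tested at 0.05/3; only if it is significant will the other two each be tested at 0.05 (Shaffer step-down; familywise error 0.05).* Add that any 98.3% intervals are descriptive and may not agree with the step-down decisions.

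In the same edit, state that the p<0.05 criterion covers the overall three-group and Mantel-Haenszel tests and not unadjusted pairwise comparisons.

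The sample size section can stay as it is, since power at 0.017 is a lower figure than the step-down gives under the planning assumptions. The change costs two or three sentences, with no effect on sample size, arms or data collection. It should be made before unblinded outcome data are analysed.
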